### 2.2. Study Processes

Immunisation providers will receive training in all study procedures, including informed consent, collection of posterior oropharyngeal swabs and 4CMenB vaccination.

Those participating via the school program will require written/electronic informed consent from the parent/guardian. Those participating via health clinics will be able to provide written consent for themselves if they are aged 16 years and above and parental/guardian consent will be required for those under 16 years. Participants and parents are provided with the contact details of the study coordinators to obtain any additional information that they may require prior to or after receiving the vaccination.

Participation includes three visits (Figure 1). During visit one, the participants will be asked to complete a one-page de-identified questionnaire to obtain information on characteristics that are known to be relevant to carriage of *N. meningitidis* including smoking/tobacco history, household size, recent respiratory tract infections and recent use of antibiotics. The immunisation providers will then obtain an oropharyngeal swab which will be placed immediately in STGG transport medium (skim milk, tryptone, glucose and glycerine; Thermo-Fisher Scientific Australia) [20] and transported to NT Pathology [21]. The immunisation provider will then administer the first dose of the licensed 4CMenB vaccine. The second visit will be scheduled a minimum of 2 months after the first visit and an SMS reminder will be sent 2 days prior to the scheduled date to notify parents/guardians/participants of the follow up visit. During the second visit, the participants will receive the second dose of the 4CMenB vaccine. The required minimal time interval between the 4CMenB vaccine and other vaccines including the COVID-19 vaccine will be maintained based on prevailing guidelines. The third visit will be scheduled 12 months after the first visit and a similar SMS reminder will be sent. During the third visit, the participants will be asked to complete the same study questionnaire that was completed at visit one and the second posterior oropharyngeal swab will be obtained. All participants will receive a $20 value voucher at visits 1 and 3 to reimburse them for their time.

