#### 2.9.2. Meningococcal Carriage Power Calculations and Impact on Disease

Assuming an overall carriage prevalence at baseline of 6.8% (B Part of it study, unpublished data), a sample size of 5239 is required in order to have 80% power to detect a 20% reduction at 12 months (alpha = 0.05, two-tailed test) or 7011 participants to have 90% power. We will recruit at least 5239 and up to 7011 participants during the study. This calculation incorporates a correlation between the baseline and 12-month measures of 0.25 (‘B Part of It’ study) and 30% loss to follow-up.

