### 3.2. Estimation of the Effect of 4CMenB on Carriage of all Neisseria Meningitidis in 14 to 19 Year Olds (12 Months Compared to Baseline)

Carriage prevalence of all *N. meningitidePPs* genogroups detected by PCR at 12 months will be compared with the results obtained at baseline using logistic regression. The difference in carriage at 12 months compared to baseline will be expressed as an odds ratio (OR) with 95% CI. Adjustments will be made for gender, age, smoking, ethnicity, remoteness area, household size (number of persons/room) as available and appropriate.

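### The carriage models in 3.2 and 4.2 leave out recent antibiotic use and recent respiratory infection, two of the four carriage-related characteristics that section 2.2 names and records at both swab visits

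*Protocol article*

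**What the plan says.** Section 2.2 gives the purpose of the one-page visit 1 questionnaire as "to obtain information on characteristics that are known to be relevant to carriage of" the meningococcus. It then names four items: "including smoking/tobacco history, household size, recent respiratory tract infections and recent use of antibiotics". At visit 3, 12 months after visit 1, "the participants will be asked to complete the same study questionnaire that was completed at visit one", and the second swab is taken at that same visit. All four items are therefore recorded alongside each swab.

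Section 3.2, one of the two primary objectives, compares the 12-month results with baseline by logistic regression. It says: "The difference in carriage at 12 months compared to baseline will be expressed as an odds ratio (OR) with 95% CI". On covariates it says: "Adjustments will be made for gender, age, smoking, ethnicity, remoteness area, household size (number of persons/room) as available and appropriate". Section 4.2 repeats this list word for word for the genogroup analyses.

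Section 4.4 uses descriptive statistics for risk-factor associations. Section 2.9.2 sizes the comparison for "80% power to detect a 20% reduction at 12 months (alpha = 0.05, two-tailed test) or 7011 participants to have 90% power", from an assumed baseline prevalence of 6.8%, a within-person correlation of 0.25 and 30% loss to follow-up.

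**The concern.** The section 3.2 odds ratio is presented as the effect of 4CMenB, yet it is a before-after contrast with no unvaccinated carriage group. Anything that affects carriage and differs between the two swab rounds is counted with the vaccine effect unless the model accounts for it.

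The two characteristics left out are those the questionnaire asks about as recent, so they describe the period just before each swab and can change from one round to the next. The article itself classes them as relevant to carriage, and both are available at both visits. No adjusted carriage analysis described in the article uses them. At stake is either a false reduction credited to the vaccine or a real reduction partly hidden.

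**Working it through.** **1. Set the two lists side by side.**

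| Characteristic named in 2.2 | Recorded at both swab visits | In the list of 3.2 and 4.2 |
|---|---|---|
| Smoking | yes | yes |
| Household size | yes | yes |
| Recent respiratory infection | yes | no |
| Recent antibiotic use | yes | no |

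**2. Reproduce the plan's sample size, to see which comparison it rests on.** Inputs from 2.9.2: p1 = 0.068; p2 = 0.8 × 0.068 = 0.0544; correlation 0.25; two-sided alpha 0.05; 30% loss.

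- Covariance = 0.25 × √(0.068 × 0.932 × 0.0544 × 0.9456) = 0.01427.
- Discordant proportions: 0.068 × 0.9456 − 0.01427 = 0.0500 and 0.0544 × 0.932 − 0.01427 = 0.0364. Their sum is 0.0865 and their difference d is 0.0136.
- Connor's formula for paired proportions: n = [1.96√0.0865 + z√(0.0865 − d²)]² / d², where z is 0.842 for 80% power and 1.282 for 90%.
- 80% power: 3667 pairs, and 3667/0.70 = 5239 (stated 5239).
- 90% power: 4908 pairs, and 4908/0.70 = 7012 (stated 7011, a rounding difference).
- The unpaired formula gives 6966 and 9323, so the stated numbers rest on the same people swabbed twice.

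**3. False change if the vaccine does nothing and only antibiotic use shifts.** The documents give no exposure figures, so the following values are assumptions. Let recent antibiotics cut the probability of detection by 70%, and let a1 and a2 be the shares with recent use at baseline and 12 months. The prevalence ratio is (1 − 0.7·a2)/(1 − 0.7·a1).

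| a1 to a2 | Ratio | Apparent change |
|---|---|---|
| 10% to 15% | 0.895/0.930 = 0.962 | −3.8% |
| 10% to 20% | 0.860/0.930 = 0.925 | −7.5% |
| 15% to 10% | 0.930/0.895 = 1.039 | +3.9% |
| 20% to 10% | 0.930/0.860 = 1.081 | +8.1% |

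The target is −20%, an odds ratio of about 0.79.

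**4. How far this depends on the assumptions.** If carriage in recent users is 0.2 to 0.6 times that in non-users, a rise from 10% to 20% gives −8.7% to −4.2%, and a rise from 10% to 30% gives −17.4% to −8.3%. If carriage with recent respiratory infection is 1.3 to 2.0 times higher, a fall in infection from 30% to 20% gives 1.06/1.09 − 1 = −2.8% to 1.2/1.3 − 1 = −7.7%.

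**5. Compare with the precision of the estimate.** With 3667 pairs, the standard error of the difference under the planned effect is √(0.0865/3667) = 0.0049, or 7.1% of 0.068. The 7.5% case is therefore about one standard error and the 3.8% case about half of one. With no vaccine effect, the chance of a significant result is about 18% and 8% respectively, instead of 5%. If use falls from 20% to 10% and the true reduction is 20%, power drops from 80% to about 46%.

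**The case against.** The strongest reply is that this is a condensed article. Section 2.10 refers to a pre-specified analysis plan that is not shown, and the covariate list ends with a qualifier about availability and appropriateness. The plan may well add the two factors. But the article gives a specific list, twice, and the qualifier governs the items listed without adding any. The point concerns what that list contains.

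A reader might infer that the article contradicts itself. It does not: nowhere does it promise to adjust for every questionnaire item, and the items also serve Table 1 objectives 13 and 14. The weakness is in the choice of covariates.

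A reader might also infer that the odds ratio will be biased by a known amount. The documents do not support that. They give no antibiotic effect, no direction for respiratory infection and no expected shift. They say only that the factors are relevant to carriage, not that they act directly on detection at the swab. Visit 3 is scheduled 12 months after visit 1, so both swabs fall in about the same season, which limits one obvious source of shift. Year-to-year change remains possible.

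Nor does it follow that gender and ethnicity are useless covariates. That holds only for complete pairs. Section 3.2 does not restrict the regression to pairs and 30% loss is allowed for, so fixed characteristics can differ in distribution between rounds if non-returners' baseline swabs are included.

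One caution about the remedy stands. Antibiotic use at 12 months is measured after vaccination. If the vaccine reduces gonorrhoea, as the study hypothesises, it could in principle also reduce antibiotic use. That is a reason to report both estimates.

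**Conclusion.** The point holds as a choice of covariates worth correcting. The adjustment list in 3.2 and 4.2 omits two short-term characteristics that the article itself calls relevant to carriage and measures at both swabs, in a contrast with no concurrent unvaccinated group. The resulting bias could go either way. Under the assumed 70% cut in detection and a change in use of 5 to 10 percentage points, it is about 4% to 8%, against the 20% reduction the study is sized for. That is half to one standard error at 3667 pairs: too small to produce a significant result reliably, but large enough to distort the error rate and the power. Smaller shifts would matter less. The sample sizes of 5239 and 7011 are unaffected.

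**What to change.** In 3.2 and 4.2:

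- Add recent antibiotic use and recent respiratory tract infection to the adjustment set, each as recorded at the visit of that swab.
- Use visit-specific values for smoking and household size.
- Keep gender, ethnicity and remoteness.
- Report the odds ratio with and without the two added covariates.
- Add a sensitivity analysis that excludes swabs taken after recent antibiotic use.

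This takes a few lines of plan wording and needs no new data collection. The costs are some loss to missing questionnaire items and the post-vaccination timing of the 12-month values, which the paired reporting makes visible. The change does not remove secular trend or ageing, so the carriage result still needs the caution due to an uncontrolled before-after comparison.

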## 4. Secondary Objectives

### 4.1. Gonorrhoea

Vaccine impact on gonorrhoea will be estimated using surveillance data from the CDC for laboratory-confirmed gonorrhoea cases, comparing six pre-vaccine surveillance years to three post-vaccination years. Interrupted time series analysis will be used to evaluate the impact through regression modelling. To estimate impact in each age group (15, 16, 17, 18, 19 years), incidence rate ratios will be estimated by comparing case numbers in the post-vaccination period with cases in the equivalent age cohort during the six pre-vaccination years. To take into account any changes over time unrelated to 4CMenB vaccination, the IRRs will be adjusted using the relevant annual gonorrhoea incidence in all adults who were not in the vaccine-eligible age cohorts.

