### 2.9. Sample Size

For ethical and equity reasons, all 14–19-year-olds in the NT in 2021–2022 will be eligible to be offered 4CMenB. The estimated eligible population is 14,077, of whom 5621 or 40% are Aboriginal or Torres Strait Islander (June 2016 estimates). We conservatively anticipate 40–50% participation of this population group and up to 30% non-return at 12 months due to factors such as interstate and intra-territory travel.

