#### 2.9.1. Gonorrhoea Infection Power Calculations

Case–control study: To assess the vaccine effectiveness of 4CMenB on gonorrhoea, assuming 1350 cases of gonorrhoea among 15–19-year-olds in the NT (Australian Bureau of Statistics) over a three year period (i.e., 450 per annum), a ratio of 3 matched controls to 1 case and assuming 50% of the eligible control population vaccinated with a correlation of 0.1, the study has at least 90% power at alpha = 0.05 to detect vaccine effectiveness of at least 20% (i.e., OR = 0.8 or less) and allowing for correlation between cases and controls on basis of 0.2. With this estimated number of cases and controls, the study is adequately powered even if 40% of the eligible population is vaccinated.

Interrupted time series study: A power simulation study that assumed three years of monthly observations post-implementation in each of the vaccinated and unvaccinated groups, constant gonorrhoea counts over time in the unvaccinated group (i.e., ~450/12 = 37.5 cases per month, so µ = 3.62), and a Poisson distribution of counts was conducted. Using the method of Feiveson with 1000 runs, the power to detect a coefficient of −0.008 in the vaccinated group as significant is 0.84 (alpha = 0.05, two-tailed test). This equates to a 9.6% reduction in cases in the vaccinated group relative to unvaccinated group (from 450 to 407 cases p.a.), assuming the two groups are of equal size.

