## 3. Primary Objectives

### 3.1. Evaluation of the Effectiveness of 4CMenB Vaccine against Gonorrhoea in 15 to 19 Year Olds

The primary analysis on vaccine effectiveness (VE) will be performed using a case–control method using controls from the sexually transmitted infections (STI) notification database for chlamydia. A case will be defined as any laboratory confirmed case of gonorrhoea among 15–19-year-olds notified to the CDC. For each case, up to four controls will be randomly sampled from a de-identified dataset of individual records extracted from the Chlamydia notification database of the CDC. Although increasing the number of controls per case increases statistical power, beyond a ratio of four controls per case only small improvements in power are expected [24,25]. A secondary case–control analysis will be performed using controls from the Australian Immunisation register (AIR). For each case, up to 20 controls will be randomly sampled from a de-identified dataset of individual records extracted from the AIR, following restriction of the database to the NT to ensure sampling from the same population. A previous similar study on assessing the effectiveness of the varicella vaccine in Australia has shown maximum precision using 20 controls per case [26]. Controls from both AIR and STI databases will be matched to cases by date of birth ± 4 weeks. Vaccination status of controls will be ascertained from the AIR after selection and vaccination considered valid if received ≥3 months before the date of laboratory confirmation of gonorrhoea in the matched case. This method of control ascertainment has been used previously to assess VE of *Haemophilus influenzae* serotype B, pertussis, varicella and measles vaccines in Australia [26]. Conditional logistic regression models will be generated in Stata to estimate VE.

VE will also be estimated using the screening method for 15–19-year-olds with laboratory-confirmed gonorrhoea within 3 months of receiving two doses of the 4CMenB vaccine. The comparator group will include all 15–19-year-olds in the NT. Using the screening method, VE will be estimated as $1-\frac{PCV(1-PCV)}{PPV(1-PPV)}$ where *PCV* is the proportion of vaccinated MenB cases and *PPV* is the vaccine coverage in the age group being analysed [27]. Vaccine coverage data for each age group will be obtained from the AIR.

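### Gonorrhoea is counted at fixed ages 15–19 for three years after vaccine was offered to 14–19-year-olds in 2021–2022, so the outcome window does not follow the eligible birth cohorts; depending on an unstated start date, 0–13% of it was never eligible, all at ages 15–16

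*Protocol article*

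**What the plan says.** All statements are in the protocol article.

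- **Who is offered vaccine.** Section 2.9: "all 14–19-year-olds in the NT in 2021–2022 will be eligible to be offered 4CMenB". No later intake is described.
- **Who counts as a case in the primary analysis.** Section 3.1: "A case will be defined as any laboratory confirmed case of gonorrhoea among 15–19-year-olds notified to the CDC". Controls are matched to cases on date of birth within 4 weeks.
- **How impact is estimated.** Section 4.1 works by "comparing six pre-vaccine surveillance years to three post-vaccination years". For the age-specific ratios: "To estimate impact in each age group (15, 16, 17, 18, 19 years), incidence rate ratios will be estimated by comparing case numbers". The comparator is "cases in the equivalent age cohort during the six pre-vaccination years". Trend adjustment uses adults outside the vaccine-eligible age cohorts.
- **Power.** Section 2.9.1 sizes the case–control study "assuming 1350 cases of gonorrhoea among 15–19-year-olds in the NT" over three years. It simulates the time series with "three years of monthly observations post-implementation in each of the vaccinated and unvaccinated groups".
- **Objectives.** Table 1 also gives the gonorrhoea population as 15- to 19-year-olds.

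The article gives no calendar date for the start of the three years. No sentence limits post-period cases to births that were eligible for vaccine.

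**The concern.** A fixed age band does not follow a cohort. The offer goes down to age 14 and outcomes start at 15, which buys one year of buffer against three years of follow-up. Once that buffer is used up, each year's new 15-year-olds, and later 16-year-olds, were too young to be offered vaccine in the programme. Their cases still count as post-vaccination. Meanwhile eligible people who turn 20 leave the outcome window.

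Two different things are at stake:

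- **Impact (secondary).** Never-eligible person-time in the post period pulls the rate ratios toward no effect. The age-15 and age-16 ratios, which the plan promises separately, are the most exposed.
- **Case–control effectiveness (primary).** A case from a never-eligible birth date has controls who are essentially all unvaccinated. Such a set contributes nothing to the conditional likelihood, so the 1350 cases may not all be informative.

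**Working it through.** **Inputs.** Eligibility at ages 14–19 in 2021–2022 and 40–50% uptake (section 2.9). Outcome ages 15–19 (sections 3.1 and 4.1). Three post years (section 4.1). 1350 cases, three controls per case, odds ratio 0.8, correlations of 0.1 and 0.2 (section 2.9.1). Assumptions of mine: uniform ages, no migration, and eligibility that rolls to the end of 2022.

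**1. The plan's own power.** I used Dupont's formula for matched sets with M controls, with p0 = coverage in controls, ψ = odds ratio, φ = correlation and q = 1 − p:

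- p1 = p0ψ / (1 + p0(ψ − 1)). For p0 = 0.5 and ψ = 0.8 this is 0.4/0.9 = 0.444.
- p0+ = p0 + φ√(q1·p0·q0/p1) and p0− = p0 − φ√(p1·p0·q0/q1).
- t_k = p1·C(M,k−1)·p0+^(k−1)·(1−p0+)^(M−k+1) + q1·C(M,k)·p0−^k·(1−p0−)^(M−k), for k = 1 to M.
- e_ψ = Σ k·t_k·ψ/(kψ+M−k+1) and v_ψ = Σ k·t_k·ψ·(M−k+1)/(kψ+M−k+1)².
- Power = Φ[(√n·|e_1 − e_ψ| − 1.96√v_1)/√v_ψ].

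With n = 1350, M = 3 and p0 = 0.5, power is 0.931 (φ = 0.1) or 0.914 (φ = 0.2). The stated figure of at least 90% is reproduced.

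**2. Never-eligible share of the 15–19 window.** People born after the end of 2008 were still under 14 when 2022 closed. They first turn 15 in January 2024. At s years after that date they occupy s of the five one-year ages. The share is the integral of s over the overlap with the window, divided by 5 × 3 = 15.

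| Start of post period | Overlap after January 2024 | Never-eligible, 3 years | By year 1 / 2 / 3 | Age 15 | Age 16 | Ages 17–19 |
|---|---|---|---|---|---|---|
| January 2021 | none | 0% | 0 / 0 / 0% | 0% | 0% | 0% |
| January 2022 | 1 year | 0.5/15 = 3.3% | 0 / 0 / 10% | 0.5/3 = 17% | 0% | 0% |
| January 2023 | 2 years | 2/15 = 13.3% | 0 / 10 / 30% | 1.5/3 = 50% | 0.5/3 = 17% | 0% |

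**3. Effect on impact.** Direct impact = uptake × effectiveness × eligible share. With 50% uptake and 20% effectiveness, the undiluted value is 0.5 × 0.2 = 10%.

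- January 2022 start: 10% × 0.967 = 9.7% overall; at age 15, 10% × 0.833 = 8.3%.
- January 2023 start: 10% × 0.867 = 8.7% overall (10% × 0.70 = 7.0% in year 3); at age 15, 10% × 0.5 = 5%; at age 16, 10% × 0.833 = 8.3%.

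**4. Effect on the case–control analysis.** In the 13.3% case, informative cases number 1350 × 0.867 = 1170. At M = 3 and 50% coverage, power is 0.894 (φ = 0.1) or 0.872 (φ = 0.2). At 40% coverage it moves from 0.916/0.897 to 0.874/0.851. The odds ratio keeps its target, because the lost sets carry no information.

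**5. Follow-up lost at 20 and over.** The eligible births span eight years (20th birthday in January 2021 to 14th birthday at the end of 2022), so three years give 8 × 3 = 24 cohort-years. At u years after January 2021, u birth-years are aged 20 or more. Integrating u over the window gives 4.5/24 = 19%, 7.5/24 = 31% or 10.5/24 = 44% for the three start dates.

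**The case against.** **Dilution is not certain.** With eligibility rolling through 2022, a January 2021 start gives none and a January 2022 start gives about 3%. The time-series power calculation counts months from implementation, which fits an early start. This stands: the overall size depends on a date that the article does not give. The zero case is not free of trouble, though. It labels as post-vaccination a period in which enrolment was still under way.

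**The wording may mean birth cohorts.** Section 4.1 refers to the equivalent age cohort and to vaccine-eligible age cohorts. The first could be read that way, and the second governs only the adjustment series. But the outcome groups are named as ages 15 to 19, and none exists for 20–22, which a birth-cohort analysis would need.

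**Ageing out does not dilute.** A reader might infer that losing vaccinated people at age 20 also pulls the estimate toward no effect. It does not. The rate at ages 15–19 is unaffected, and these people are kept out of the adjustment series. Only information is lost.

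**The primary result is safe from bias.** A reader might infer that the main effectiveness estimate is diluted too. Matching on date of birth prevents that. Section 3.1 also allows up to four controls per case. At 4:1 with 1170 cases the formula above gives 0.914 or 0.897, so the power shortfall is small.

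**A fixed age band is a legitimate target.** Impact on notification rates at ages 15–19 can be reported as a population quantity, and Table 1 sets it so. That supports keeping it as a labelled analysis. It does not make the age-15 ratio a measure of the vaccine's effect when up to half of its person-time was never eligible.

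**The full protocol or analysis plan may settle this.** The start date may well be given there. But the article itself fixes the outcome ages, and that is what needs changing.

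**Conclusion.** The mismatch between the eligible cohort and the outcome window is real. Its effect on the results is moderate and conditional. Under rolling eligibility, 0%, 3.3% or 13.3% of 15–19 person-time is never eligible, all at ages 15 and 16. The bias falls on the secondary impact estimates, chiefly the age-15 and age-16 ratios. In the least favourable of these cases the direct overall impact is 8.7% instead of 10%, and the age-15 effect is halved. The primary case–control estimate loses some precision and is not biased.

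These sizes assume uniform ages, because the article gives no cases by single year of age. If cases concentrate at 17–19, the overall dilution and the loss of informative cases are smaller, but the shares within ages 15 and 16 remain. That the programme was a single round is inferred from section 2.9. If eligibility were instead frozen at one early date and counting began late, the shares would be larger, but the two-year eligibility period in section 2.9 does not suggest that. This is worth changing, but it is not a fatal flaw.

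**What to change.** 1. State the calendar start of the three post-vaccination years.
2. In the case–control and screening analyses (section 3.1), include every laboratory-confirmed case in the period from a vaccine-eligible birth cohort, including people who have turned 20. Take controls and coverage from the same births.
3. In section 4.1, compute age-specific rate ratios only for age-by-year cells whose births were eligible, against the same ages in the six pre-vaccine years. Because the age mix then shifts through the post period, use age-specific modelling or standardisation in the time series.
4. Keep the fixed 15–19 analysis as a sensitivity analysis and align Table 1.

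Cost: a wider age range in the same surveillance and immunisation-register extracts, some extra modelling, and results no longer labelled strictly as 15–19-year-olds, which changes the population named in the primary objective.

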### 2.3. Patient and Public Involvement

The study materials will be reviewed by a Youth Advisory Group and an Aboriginal Advisory Group at several stages. Public, Independent, Catholic, Christian and Lutheran schools in the NT will provide information to parents/guardians and students and support the roll out of the study in schools. The ACCHOs will provide information about the study to their communities and support the roll out in clinics. A multimedia communication strategy has been developed by a public relations/communications company in collaboration with the media team of the University of Adelaide. Key strategies include website development (B Part of it NT. Available online: bpartofitnt.com.au (accessed on 17 January 2022)), brand identity ‘B Part of it NT’, a Facebook page, advertising and creating supporting material in English and up to 10 Aboriginal languages to be used in remote settings, a flip chart explaining the study in a simplified version to be used alongside the participant information sheets, ambassador engagement, public relations and management and media training. Participants and parents are encouraged to provide feedback on the study using the B Part of it NT Facebook page.

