### 2.8. Data and Statistical Analysis Plan

Basic demographic data and risk factors for meningococcal disease (from the questionnaire), laboratory results and vaccination data will be entered into the study database. IMD and gonorrhoea rates will be obtained from routine surveillance data from the CDC, NT. For the case–control and screening method analyses, data custodians from AIR and CDC NT will link participant records and assign unique study IDs prior to sending data to the study team. No identifying information will be stored in the main study database. Infection rates for IMD and gonorrhoea for various demographic subgroups will be estimated from CDC NT surveillance data, and a many-to-one merge will be used to link background rates to individual records, so as to adjust for these rates in the subsequent analyses.

There are some limitations for observational studies with potential for bias and confounding. Some of the potential sources of bias identified include, any changes to the current practice of notifications over the study period, differences in case ascertainment due to variation in extent of screening and contact tracing, differences in healthcare seeking behaviour for STI treatment and vaccination, extent of other STI prevention/health promotion programs offered in the region, missing data, misclassification of the outcome, differences in lab diagnostics and those lost to follow up during the study period.

To partly mitigate the effects of some of the potential biases, different study designs will be utilized in the investigation of the research hypotheses. This approach will aid in triangulation of findings and strengthen the conclusions that will be drawn from the study [23]. Since there is considerable debate about the circumstances under which causality can be tested or assumed, we will use two different approaches with differing and unrelated key sources of potential biases in assessing vaccine effectiveness. The two are the screening approach and the case–control approach. In the screening approach, results are compared between different populations in different contexts (cross-context comparisons). In the case–control approach, two different control groups will be used, namely controls from the STI notification (Chlamydia) database and the Australian Immunisation register (AIR). These approaches will not give the same estimates of the causal effect unless all analyses are unbiased.

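### The gonorrhoea impact IRRs are adjusted only for adult gonorrhoea incidence, which cannot remove a change in testing or ascertainment specific to 15–19-year-olds

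*Protocol article*

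**What the plan says.** Section 4.1 (Gonorrhoea, under Secondary Objectives) fixes three things.

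- **Data.** "Vaccine impact on gonorrhoea will be estimated using surveillance data from the CDC for laboratory-confirmed gonorrhoea cases". The periods are given by the phrase "comparing six pre-vaccine surveillance years to three post-vaccination years".
- **Contrast.** For each single year of age from 15 to 19, "incidence rate ratios will be estimated by comparing case numbers in the post-vaccination period with cases in the equivalent age cohort" before vaccination.
- **Adjustment.** For changes over time that are not due to the vaccine, "the IRRs will be adjusted using the relevant annual gonorrhoea incidence in all adults who were not in the vaccine-eligible age cohorts". The section names no other adjustment.

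Section 2.8 includes "differences in case ascertainment due to variation in extent of screening and contact tracing" in its list of possible biases, with changes in notification practice, care-seeking, other STI programmes and laboratory diagnostics. It says that different designs will partly mitigate some of these. It then says "we will use two different approaches with differing and unrelated key sources of potential biases in assessing vaccine effectiveness", and names the screening and case–control approaches. The background rates that section 2.8 merges into individual records are infection rates, not testing rates.

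Section 3.1 already uses chlamydia notifications. The primary case–control analysis samples its controls from "a de-identified dataset of individual records extracted from the Chlamydia notification database of the CDC".

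A same-age comparison also exists. The time-series power calculation in section 2.9.1 assumes monthly counts in a vaccinated and an unvaccinated group, and Table 1, objective 3, lists 15–19-year-old notifications in vaccinated against unvaccinated people.

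**The concern.** A notification needs a test, so a notification count is the product of infection and ascertainment. A before–after ratio of counts reflects a change in either. Adult incidence is a reasonable control for what moves both age groups together, such as a new assay or a territory-wide change in reporting. It carries no information on a change confined to ages 15–19, for instance in youth screening or contact tracing.

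If such a change began near the start of vaccination, the six earlier years could not separate it from vaccine impact. A relative fall in testing would look like benefit, and a relative rise would hide benefit. The adjusted IRR would give no sign of either.

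**Working it through.** **1. Inputs.** Section 2.9.1 gives 450 gonorrhoea cases a year at ages 15–19 (1350 over three years). Section 4.1 gives six years before and three after. At a constant rate this is 6 × 450 = 2700 cases before and 3 × 450 = 1350 after. The documents give no testing data and no chlamydia count, so both are assumed below.

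**2. The plan's own figure.** The 9.6% in section 2.9.1 reproduces as 12 × 0.008 = 0.096, and 450 × 0.904 = 406.8, the stated 407. It comes from a slope in a vaccinated-against-unvaccinated simulation. It is not a before–after IRR and is not used as a benchmark here.

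**3. Form of the bias.** Let r be the post/pre change in ascertainment at 15–19 divided by the same change in adults. Then

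adjusted IRR = true IRR × r.

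A change shared with adults has r = 1 and drops out. Otherwise:

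- true IRR 1.00, r = 0.90: 0.90, read as a 10% reduction
- true IRR 0.90, r = 1.10: 0.99, so the effect almost disappears
- true IRR 0.80, r = 1.25: 1.00, so the effect disappears

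**4. Standard errors**, for Poisson counts and an error-free adult series:

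- pooled 15–19: √(1/2700 + 1/1350) = 0.033
- one year of age, if cases split evenly (540 before, 270 after): √(1/540 + 1/270) = 0.075

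**5. Chance of a significant result with no vaccine effect.** With z = |ln r| / SE, the probability is Φ(z − 1.96) + Φ(−z − 1.96).

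| r | Pooled: z | Pooled: probability | Single year: z | Single year: probability |
|---|---|---|---|---|
| 0.95 | 1.54 | 34% | 0.69 | 11% |
| 0.90 | 3.16 | 89% | 1.41 | 29% |

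At r = 0.90 the expected 95% interval is 0.84 to 0.96 pooled. For a single year it is 0.90 × exp(±1.96 × 0.0745), or 0.78 to 1.04. The bias in the estimate is the same; only the chance of significance differs.

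**6. With a same-age chlamydia series.** The ratio (gonorrhoea IRR) / (chlamydia IRR) cancels r if a testing change affects both infections alike and nothing else changes chlamydia. For C chlamydia notifications a year, pooled SE = √(1/2700 + 1/1350 + 1/(6C) + 1/(3C)), and the smallest significant reduction is 1 − exp(−1.96 × SE).

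| Assumed C | SE | Smallest significant reduction |
|---|---|---|
| none (no control series) | 0.033 | 6.3% |
| 1350 | 0.038 | 7.3% |
| 900 | 0.041 | 7.7% |
| 450 | 0.047 | 8.8% |

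**The case against.** Several points on the other side are sound.

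- **A same-age comparison is planned.** In the vaccinated-against-unvaccinated contrast of section 2.9.1 and Table 1, a testing change common to both groups would largely cancel, so it would be wrong to say that the plan has no same-age comparator. But that contrast does not adjust the IRR in section 4.1, and it is exposed to differences in care-seeking by vaccine status.
- **The mechanism is conjecture.** A reader might infer that the programme itself will alter testing, since section 2.3 says: "A multimedia communication strategy has been developed by a public relations/communications company". The documents do not support this. The visits described in section 2.2 include no STI test, and nothing in section 2.3 says that the campaign promotes testing. No direction of change is supported either.
- **The larger probabilities are for pooled counts.** Section 4.1 describes single-year-age IRRs, for which 11% and 29% are the nearer figures under an even split. Overdispersion and error in the adult series would lower the chance of false significance further.
- **An annual adjuster is not itself a fault.** The IRR contrasts multi-year periods, and no bias from within-year variation has been shown.
- **The risk is disclosed, and the objective is secondary.** The primary case–control analysis with chlamydia controls is not touched by this point.
- **Details may sit in the analysis plan, which is not shown.** That would answer a complaint about omission. Here the article itself states the adjuster.

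What stands is that the stated adjuster cannot deal with an age-specific change, and that the mitigation named in section 2.8 does not reach this IRR.

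**Conclusion.** The point holds as a conditional bias in a secondary analysis. The adult series corrects the IRRs only for changes shared with adults, and any relative change in ascertainment at 15–19 multiplies the IRR directly. A 10% relative fall turns a true IRR of 1.00 into 0.90, falsely significant about 89% of the time pooled or 29% for a single year of age.

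These figures assume notifications proportional to testing, 450 cases a year throughout, Poisson counts, an error-free adult series and, for single years, an even split. The 10% is illustrative.

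A reader might set that 10% beside the 9.6% in section 2.9.1 and conclude that it would erase the effect for which the study is sized. That does not follow, because the 9.6% belongs to a different estimand.

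**What to change.** Keep the adult-adjusted IRR as planned. Pre-specify, before post-programme data are examined, a sensitivity analysis with chlamydia notifications in the same ages and periods as a concurrent control series, taken from the CDC database that already supplies the case–control controls. Model gonorrhoea relative to chlamydia, for example through an infection-by-period interaction, and report the result beside the adult-adjusted IRR. Interpret disagreement as possible ascertainment change. A formal rule that both must agree is not advised, as there is no evident threshold for agreement.

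The cost is one aggregate extract and one further model. Precision falls: the pooled SE of log IRR rises from 0.033 to about 0.038–0.047 for an assumed 1350 to 450 chlamydia notifications a year. Chlamydia testing is an imperfect proxy for gonorrhoea testing. The added analysis may also share weaknesses with the chlamydia-control effectiveness analysis, and so be less independent of it than section 2.8 intends. For both reasons it should stand beside the planned IRR and not replace it.
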